#### Secondary endpoints

For the secondary clinical endpoints we will compare: (i) mean haemoglobin concentration in children at the end of the transmission season, (ii) incidence of malaria defined by history of fever or temperature of ≥37.5°C and a *P. falciparum *parasitaemia cut-off defined to give optimum sensitivity and specificity in this setting, (iii) parasite prevalence in children at the end of the transmission season, (iv) number of children with enlarged spleens at the end of the transmission season. In general, all quantitative outcomes will be compared using appropriate summary statistics, such as mean differences or risk ratios. Hypothesis testing will be based on a two sample unpaired t-test, adjusting for possible co-variates. If the data do not satisfy normality and constant variance assumptions, an appropriate non-parametric test will be used. Both linear regression (for continuous variables such as haemoglobin levels) and logistic regression (for dichotomous variables such as presence or absence of parasitaemia) will be used to quantify the group differences allowing for individual level covariates (such as age, house design, bed net use) using random effects to allow for clustering.

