### Design

A cluster-randomized controlled study design will be used, as IRS is a community-level intervention and the village cluster as a suitable unit for randomization. All households in all the clusters will be offered LLIN at no cost to the recipients to enable all residents to benefit from this intervention. The clusters will then be randomized into two equal groups; all households in the villages in one group will be offered IRS and those in the other group will not. It is not possible to conduct the IRS in a blinded manner since a placebo would quickly be identified by the community as non-protective. To assess whether DDT IRS and LLINs combined provide better protection against clinical malaria in children than LLINs alone, 75- 125 children aged from 6 months to 13 years old will be sampled according to cluster size enrolled into a study cohort. These children will be followed during the malaria transmission season in 2010 and 2011. Clinical malaria will be recorded by study staff using PCD in close collaboration with government health workers both at the village and health facility levels. Parasites will be detected by a rapid diagnostic test (RDT, Paracheck Pf, Orchid Biomedical Systems, Goa, India) and treatment will follow government treatment guidelines.

The study cohort will be surveyed for malaria indices (parasite prevalence, anaemia and spleen rate) at the end of both transmission seasons to generate data for the secondary endpoints and also at baseline before the year 1 transmission season. Baseline data will be used to compare the 2 groups before the interventions and end of season survey data will be used to attempt to define a *Plasmodium falciparum *parasitaemia cut-off giving optimum sensitivity and specificity for malaria cases in this setting [14].

Exposure to malaria vector mosquitoes and parasites indoors will be assessed using CDC light traps and window traps every 4 weeks from June to December and every 8 weeks from January to May in at least 6 randomly selected households in 16 village clusters in each arm of the study. This will be followed by detection of *Anopheles gambiae *species, parity status and sporozoite infection. A schematic representation of the trial is shown in Figure 1.

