### Randomisation

An equal number of clusters will be randomized to receive IRS, in addition to the LLINs provided to all enrolled households, and in these all households will be treated. In cluster-randomised controlled trials it is particularly important to minimize imbalance for factors known to be highly correlated with the disease outcome; in this case age and access to health facilities and location. At the village level we will stratify by presence of a primary health care centre (PHC) and geographical location by dividing the total area into four with two of equal area on each bank of the river. Stratification for PHCs will also ensure that the larger villages are evenly distributed in the experimental groups. In addition, balanced randomization will be used to ensure that children of similar ages are enrolled at the village level.

Stratified randomisation of villages to the study groups, as outlined above, will reduce the likelihood of chance imbalances between study arms but as only relatively small number of units can be randomized in such a cluster design, both groups cannot be assumed similar for all factors. Baseline data on spleen rates, parasite prevalence and anaemia will be collected on a representative sample of enrolled children in each village at the beginning of the main transmission season in 2010 to assess imbalances in malaria at village level.

Observer bias will be reduced where feasible. Blood films will be read by microscopists blinded to the identity and intervention status of the subjects. Mosquito collector bias will be reduced by using standard light traps and exit traps, which do not rely on the ability of the fieldworker to collect specimens. Trap catches will be examined by a different person to the trap collector and they will be blinded to the trap location. The processes of the interventions, both for LLINs and IRS, will be closely monitored not only for quality but also to document any bias between the villages.

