**Figure 2 F2:**
[figure not shown]
**Sample size estimations at varying effect, incidence and coefficient of variation (CV)**.

Data from the same cluster trial quoted above was used to explore sample size considerations for the parasitological and anaemia, endpoints. Considering parasitaemia as a proportion and haemoglobin as a concentration with 35 clusters of 110 children each suggested that sampling half the child cohort would have 80% power to detect a 30% reduction in parasitaemia and a 0.5 mg/mL reduction in haemoglobin at 95% confidence.

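### Baseline village values of the secondary outcomes are collected, but the secondary analysis does not commit to adjusting for them, which forgoes some precision

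*Protocol article*

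**What the plan says.** The Design section lists spleen rate, anaemia and parasite prevalence as the survey measures and places the surveys "at the end of both transmission seasons to generate data for the secondary endpoints and also at baseline before the year 1 transmission season". The Randomisation section adds: "Baseline data on spleen rates, parasite prevalence and anaemia will be collected on a representative sample of enrolled children in each village". Under Clinical evaluations, at least 50 children per cluster are finger-pricked at the surveys, and anaemia is assessed as haemoglobin concentration.

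Two uses of the baseline values are stated. Design: "Baseline data will be used to compare the 2 groups before the interventions". Randomisation: "to assess imbalances in malaria at village level". The Randomisation section also concedes, because few units are randomised, that "both groups cannot be assumed similar for all factors".

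Under Secondary endpoints in the Analytical plan, the outcomes are end-of-season haemoglobin, parasite prevalence and spleen enlargement, plus malaria incidence under a parasite cut-off. "Hypothesis testing will be based on a two sample unpaired t-test, adjusting for possible co-variates". Linear and logistic regressions then follow, "allowing for individual level covariates (such as age, house design, bed net use) using random effects to allow for clustering". For the primary outcome, the same plan says that linear regression on cluster rates can adjust for cluster-level covariates. The secondary section has no such statement.

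**The concern.** Villages that start with low haemoglobin or high parasite prevalence may tend to end the season that way. To the extent that they do, part of the between-village variance in the end-of-season outcome is predictable from data already in hand. A model that leaves the baseline value out keeps that variance in its error term. It also leaves any chance difference between the arms at baseline in the realised treatment difference.

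The stake is precision on the secondary clinical endpoints. There is also a question of discipline. The plan intends to look at baseline imbalance and leaves the covariate list open, in a trial where spraying cannot be blinded. The choice to adjust could then be made after the data are seen.

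**Working it through.** **Inputs from the article.** 35 clusters per arm and an average of 110 children per cluster, half of them sampled (about 55; at least 50 under Clinical evaluations). Between-cluster coefficient of variation k = 0.31 to 0.43, stated for the incidence calculation. Secondary power, from the text after Figure 2: "sampling half the child cohort would have 80% power to detect a 30% reduction in parasitaemia", with 0.5 mg/mL for haemoglobin.

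**Not in the article, so assumed.** Control prevalence, haemoglobin SD, intracluster correlation (ICC), and rho, the within-arm correlation between a village's baseline and end-of-season values.

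**1. The stated 80%.** It cannot be reproduced without those inputs, so only its plausibility can be checked.

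- Parasitaemia: power = Φ(√[(c−1)(p0−p1)²/v] − 1.96), with v = [p0(1−p0)+p1(1−p1)]/m + k²(p0²+p1²), c = 35 and m = 55. At p0 = 10%, p1 = 7% and k = 0.31, v = 0.00282 + 0.00143 = 0.00425. Then √(34 × 0.0009/0.00425) = 2.68 and power is 76.5%. It is 64.9% at k = 0.43. At p0 = 20% the two values are 92.0% and 78.7%. Power of 80% is reached at a prevalence of 11% (k = 0.31) to 22% (k = 0.43), so the figure is plausible for parasitaemia.
- Haemoglobin: the detectable difference is 0.14 to 0.57 g/dL for an SD of 1.2 to 1.8 g/dL and an ICC of 0.01 to 0.20. The stated 0.5 mg/mL is literally 0.05 g/dL, below that whole range, so the unit needs checking. The gains below do not depend on it; they start from the nominal 80%.

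**2. Gain from adjusting for the village baseline.** The variance is multiplied by 1−rho², the interval width by √(1−rho²), and power becomes Φ(2.80/√(1−rho²) − 1.96). The equivalent number of clusters is 35/(1−rho²).

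| rho | variance | interval width | power | equivalent clusters per arm |
|---|---|---|---|---|
| 0 | 1.00 | 1.000 | 80.0% | 35.0 |
| 0.2 | 0.96 | 0.980 | 81.6% | 36.5 |
| 0.3 | 0.91 | 0.954 | 83.6% | 38.5 |
| 0.4 | 0.84 | 0.917 | 86.4% | 41.7 |
| 0.5 | 0.75 | 0.866 | 89.9% | 46.7 |

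The cost of one extra term with 70 clusters is a variance factor of about 1 + 1/(70−4) = 1.015, or 1.5% if rho is zero.

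**3. How large rho can be for parasite prevalence.** Sampling error in a village prevalence limits the observable correlation. With perfect persistence and equal prevalence p at both surveys, the maximum rho is k²p²/[k²p² + p(1−p)/50]. At p = 10% and k = 0.31 this is 0.000961/(0.000961 + 0.0018) = 0.35.

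| prevalence | maximum rho (k 0.31 to 0.43) | rho if true persistence is 0.5 |
|---|---|---|
| 5% | 0.20 to 0.33 | 0.10 to 0.16 |
| 10% | 0.35 to 0.51 | 0.17 to 0.25 |
| 20% | 0.55 to 0.70 | 0.27 to 0.35 |

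The last column gives power gains of about 0.4 to 5 points. For haemoglobin with an assumed ICC of 0.05, the reliability of a village mean of 50 is 2.5/3.45 = 0.72. An observed rho of 0.5 then needs a true correlation near 0.7.

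**4. Chance imbalance.** The baseline difference between arms has SD √(2/35) = 0.24 village-level SDs, with a 95% range of ±0.47. The difference detectable at 80% power is 2.80 × 0.24 = 0.67 SDs. An imbalance at the edge of the range shifts the unadjusted estimate by rho × 1.96/2.80 of that difference: 21% at rho 0.3 and 35% at rho 0.5.

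**5. Timing of the baseline survey.**

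- Design: before the transmission season and before the interventions.
- Randomisation: at the beginning of the main transmission season.
- Study area and participant eligibility: enrolment in June 2010, with survey and interventions within the same two months.
- Study procedures and evaluations: spraying and net distribution intended to be complete in May.
- Table 1: spraying in May and June 2010, first clinical survey in June.

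These statements do not establish that the survey came before spraying in each sprayed village.

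**The case against.** A reader might infer that the plan analyses the secondary outcomes without baseline values. The text does not go that far. The t-test sentence allows for possible covariates and the regression list is given only as examples, so baseline adjustment remains open. The article also condenses a fuller protocol, and an analysis plan not shown may fix the covariates. This stands, and it reduces the point to a missing commitment. The point survives because the article itself describes the secondary analysis, names example covariates and states what the baseline data are for, and adjustment appears in none of these places.

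A reader might also infer that the unadjusted comparison is biased. It is not: under randomisation, here stratified by primary health care presence and location, chance imbalance adds variance and conditional error only.

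The strongest objection concerns size. No correlation is given, and the article offers reasons to expect a modest one. Transmission is highly seasonal. The baseline survey is in June and follow-up in November to December. All clusters are offered nets and half are sprayed around that time. National spraying took place in 2009, and children found ill or anaemic at surveys are treated. With the sampling limit in step 3, a gain of 10 points cannot be taken as the expected value. This stands too.

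Finally, adjustment could itself do harm if the survey followed spraying. That is a valid condition on the fix.

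**Conclusion.** The point holds as a missing commitment on the secondary clinical endpoints that the baseline survey measures. The values are collected, their stated use in comparing the arms is descriptive, and the models neither name nor exclude them. The consequence is lost precision and conditional error from chance imbalance.

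From a nominal 80% power, adjustment gives about 82%, 84% and 90% at rho 0.2, 0.3 and 0.5, with intervals about 2%, 5% and 13% narrower. At low parasite prevalence the lower end is the realistic one. If rho is zero the cost is about 1.5% of variance. These figures rest on a normal approximation, village-level covariance adjustment and an assumed rho. They also require a baseline survey that preceded spraying, which the article's dates leave unsettled. The primary endpoint is not affected.

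**What to change.** First reconcile the timing statements in Study area and participant eligibility, Design, Randomisation, Study procedures and evaluations, and Table 1. Record for each sprayed cluster whether the 2010 baseline survey preceded spraying. Use the covariate only if it did.

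On that condition, add to the Secondary endpoints section that each linear or logistic random-effects model for haemoglobin, parasite prevalence and spleen enlargement includes the village baseline value of the same outcome (mean haemoglobin, parasite prevalence or spleen rate) as a fixed covariate. State that this is the main secondary analysis and fix it before outcome data are compared by arm. The unadjusted comparison can be reported beside it.

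A village value suits this design better than a child's own value, because only a sample is finger-pricked at each survey and children are replaced in year 2. Where the same child was measured at both surveys, the child's own baseline haemoglobin can be used in a sensitivity analysis.

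The cost is a few sentences of plan text, one model term per endpoint and a check of survey and spraying dates. No new data are needed.

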### Timetable of activities

The timetable of activities is shown in Table 1.

**Table 1 T1:** Timetable of activities

Activity	J	F	M	A	M	J	J	A	S	O	N	D
2010												

Senior staff recruitment	X											

Ethical approval	X	X										

Order and shipment of equipment		X	X	X								

Field staff recruitment & training			X	X								

Training of sprayteams, planning IRS				X								

Sensitisation of study population			X	X	X							

Enumeration & house selection for entomology						X						

House spraying & LLIN distribution					X	X						

Selection subjects, PCD, & travel monitoring						X	X	X	X	X	X	

Entomological surveys						X	X	X	X	X	X	

Clinical & bednet surveys						X					X	X

Data programming and entry					X	X	X	X	X	X	X	X

2011												

Steering Group Meeting in The Gambia			X									

ELISA and PCR assays	X	X	X									

Data entry cleaning & report writing	X	X	X	X								

Sensitisation of study population			X	X								

House selection for entomology				X	X							

House spraying & LLIN distribution					X	X						

Replace subjects, PCD & travel monitoring						X	X	X	X	X	X	

Entomological surveys						X	X	X	X	X	X	

Cost data collection									X	X		

Clinical & bednet surveys											X	X

Data analysis											X	X

Data entry						X	X	X	X	X	X	X

2012												

Data entry, cleaning & analysis	X	X	X	X								

Steering Group Meeting in the UK				X								

Report findings to study communities					X							

Data analysis & report writing					X	X	X	X	X			

Cost effectiveness analysis					X							

Final report to the Steering Committee										X		

Report findings to Gambian Government											X	

Scientific paper writing			X	X	X	X	X	X	X	X	X	

### Ethical approval

This study is conducted in accordance with the principles set forth in the ICH Harmonised Tripartite Guideline for GCP and the Declaration of Helsinki in its current version, whichever affords the greater protection to the participants. It was approved by the Gambian Government/MRC Laboratories Joint Ethics Committee first approved on the 12th August 2008 (ref: L2009.15, L2010.19; SCC1128) and the London School of Hygiene and Tropical Medicine Ethics Committee approved on the 16th September 2009 (ref: 5592).

## Discussion

As enthusiasm for malaria control in Africa gathers pace, there is an urgent need to evaluate the effectiveness of multiple interventions. This study evaluates the efficacy of the 2 most common vector control tools used for malaria control: IRS and LLINs. This study sets out to examine whether there is an additional benefit of using IRS in combination with LLINs compared to current best practise, the use of LLINs alone. It is designed to measure whether the double intervention will provide greater protection against malaria incidence by substantially reducing transmission.

The main morbidity outcome will be incidence of clinical disease assessed using PCD. PCD is considered to generate information of more direct relevance to public health than active case detection and is thus more suitable for evaluating population level malaria interventions [16]. It is especially relevant as many African countries, the Gambia included, have launched policies that malaria should be eliminated as a public health problem. All the clinical outcomes will be measured in a cohort of children aged 6 months to 13 years of age following the age pattern of disease and infection in this area. In areas of high malaria transmission the main burden of paediatric malaria is borne by children under 5 years old, but this pattern shifts to include older children and adolescents in areas with lower levels of transmission for example Ndiop in Senegal and the Farafenni area of The Gambia [17,33]. This trend is increasing as malaria decreases for example a recent study in the Gambia and Guinea Bissau, which included a site in the URR, found parasite prevalence highest in the 11 - 15 years olds [34]. The lower limit of 6 months has been selected in the current study for cultural and clinical reasons and the upper limit corresponds to the age when most children move to middle schools (Upper Basic) which are often further away from their village. In addition to quantifying malaria incidence and parasite prevalence we will measure anaemia in both the community surveys and at the time of clinical attacks and all subjects with Hb < 8 gm/dL will receive treatment. In addition to the clinical benefit, malaria is a major risk for anaemia in these populations [35], as other causes, such as hookworm infection are infrequent, and documented changes in anaemia will complement the main outcomes.

There are no apparent risks to the safety of individuals or communities in the use of these interventions. Permethrin-treated long lasting nets and DDT-WP have been fully evaluated by the WHO Pesticide Evaluation Scheme and approved for vector control [11]. The biggest hazard associated with the trial is the leakage of insecticide, particularly DDT, into the external environment. National guidelines for insecticide transport, storage and all operational procedures will be strictly followed to ensure that this remains unlikely. However, in The Gambia about 5% of rural traditional houses are destroyed each year during the rains [36], suggesting that some DDT may become disseminated into the environment.

LLIN are similarly beneficial at the individual level, and at the community level where high coverage is attained. However, in The Gambia no community protection has been found with ITNs [37-39] as it has in other parts of Africa [40,41]. Study children will benefit from a health check at the surveys and at both the village and health facility levels clinical services will be supported by training and the presence of study nurses in addition to government staff.

It is also important that the correct normal practice of parents/carers in the case of their child becoming sick is not altered in a detrimental fashion by their child being enrolled in the study. For example a parent/carer may delay taking a child to the nearest health facility/post if they think that a study nurse is visiting their village the next day. Both the provision of fares when a children reports sick at a health facility and emphasis of the vital role of parent/carers during enrolment and the conduct of the study will help to mitigate against this.

There is currently a rush for DDT IRS in many African countries, yet we lack the evidence of the protective efficacy of this intervention against clinical malaria. To date, most trials have been non-randomised and, often non-controlled, making it difficult to evaluate protective efficacy [42]. The proposed trial is urgently needed to inform policy makers of any additional benefit of using IRS with DDT together with current best practice (LLINs). Indeed this is considered a priority area of research by Roll Back Malaria (http://www.rollbackmalaria.org). The trial will benefit our collaborators at the NMCP in The Gambia by providing capacity building: developing management systems, resistance monitoring strategies and providing training on IRS according to the principles laid down by WHO [43]. This is particularly timely since a major IRS programme with DDT is underway. The findings from this study will provide valuable information to inform policy decisions, both in this region and elsewhere, regarding how best to use scarce health care resources to control malaria most effectively.

## Abbreviations

**CDC**: Centers for Disease Control and Prevention; **CRF**: Case report form; **CV**: coefficient of variation; **DDT**: Dichloro-diphenyl-trichloro-ethane; **EC**: Ethical committee; **EIR**: Entomological inoculation rate; **GCP**: Good clinical practice; **GLLAMM**: Generalized Linear Latent and Mixed Models; **ICH**: International conference on harmonisation of technical requirements for registration of pharmaceuticals for human use; **ID**: Identification; **IRS**: Indoor residual spraying; **ITN**: Insecticide Treated Net; **LLINS**: Long lasting impregnated nets; **LSHTM**: London School of Hygiene and Tropical Medicine; **MRC**: Medical Research Council; **NMCP**: National malaria control programme; **PCD**: Passive case detection; **PCR**: Polymerase chain reaction; **PI**: Principal Investigator; **PHC**: Primary Health Care; **RDT**: Rapid Diagnostic Test; **SAE**: Serious Adverse Event; **URR**: Upper River Region; **VHW**: Village health worker; **WHO**: World Health Organisation; **WHOPES**: Who Pesticide Evaluation Scheme
